## **9 CHANGES TO PLANNED ANALYSIS FROM STUDY PROTOCOL**

An additional sensitivity analysis targeting treatment policy where response is analyzed regardless of intercurrent events will also be performed on the primary endpoint.

The sensitivity estimand will also include subjects who discontinued due to adverse events.

Logistic regression estimator approach for population-level difference of proportions will be used instead of logistic regression with multiple covariates.

Composite endpoints for ACR+PASI are added.

LOCF/NRI analysis is added for responder parameters and LOCF for continuous.

BASDAI derivation is re-calculated according to SAP.

11 APPENDICES

Appendix A: HAQ-DI

HEALTH ASSESSMENT QUESTIONNAIRE

Name \_\_\_\_\_ Date \_\_\_\_\_

In this section we are interested in learning how your illness affects your ability to function in daily life. Please feel free to add any comments on the back of this page.

Please check the response which best describes your usual abilities OVER THE PAST WEEK:

|                                                                | Without
ANY
Difficulty | With
SOME
Difficulty | With
MUCH
Difficul
ty | UNABLE
To Do |
|----------------------------------------------------------------|------------------------------|----------------------------|--------------------------------|-----------------|
| DRESSING & GROOMING                                 |                              |                            |                                |                 |
| Are you able to:                                               |                              |                            |                                |                 |
| - Dress yourself, including tying shoelaces and doing buttons? | _____                        | _____                      | _____                          | _____           |
| - Shampoo your hair?                                           | _____                        | _____                      | _____                          | _____           |
| ARISING                                                 |                              |                            |                                |                 |
| Are you able to:                                               |                              |                            |                                |                 |
| - Stand up from a straight chair?                              | _____                        | _____                      | _____                          | _____           |
| - Get in and out of bed?                                       | _____                        | _____                      | _____                          | _____           |
| EATING                                                  |                              |                            |                                |                 |
| Are you able to:                                               |                              |                            |                                |                 |
| - Cut your meat?                                               | _____                        | _____                      | _____                          | _____           |
| - Lift a full cup or glass to your mouth?                      | _____                        | _____                      | _____                          | _____           |
| - Open a new milk carton?                                      | _____                        | _____                      | _____                          | _____           |
| WALKING                                                 |                              |                            |                                |                 |
| Are you able to:                                               |                              |                            |                                |                 |
| - Walk outdoors on flat ground?                                | _____                        | _____                      | _____                          | _____           |
| - Climb up five steps?                                         | _____                        | _____                      | _____                          | _____           |

Please check any AIDS OR DEVICES that you usually use for any of these activities:

[figure not shown]

- |                                     |                                                                                                             |
|-------------------------------------|-------------------------------------------------------------------------------------------------------------|
|  Cane       |  Devices used for dressing (button hook, zipper pull, long-handled shoe horn, etc.) |
|  Walker     |  Built up or special utensils                                                       |
|  Crutches   |  Special or built up chair                                                          |
|  Wheelchair |  Other (Specify: _____)                                                             |

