#### **8.6.2.4 Health Assessment Questionnaire (HAQ-DI)**

The health assessment questionnaire (HAQ-DI) is a twenty-item PRO instrument which assesses current physical function/disability. It covers 8 categories (dressing and grooming, hygiene, arising, reach, eating, grip, walking and common daily activities). There are 4 response options ranging from 0 (no difficulty) to 3 (unable to do) (See [Appendix A](#)).

To calculate the HAQ-DI, the highest sub-category score determines the value for each category, unless aids or devices are used. There must be at least 6 out of 8 categories answered or else the score cannot be calculated. Each category scored is averaged into an overall HAQ-DI score ranging from 0 to 3.

The aids used for adjustment by category are: dressing – devices used for dressing; rising – built up or special chars; eating – built up or special utensils; walking – canes, walkers or crutches; hygiene – raised toilet seats, bathtub seats, bathtub bars, long handles appliances in bathroom; reach – long-handled appliances for reaching; and grip – jar openers.

If an aid is required for any category, or another person is required to help for any category then that category score increases a score of 0 or 1 to a 2. Scores already at 2 and 3 are not modified. Aids and devices considered recorded in the ‘other’ category will not be considered in the analysis.

Scores of 0 to 1 represent mild to moderate disability, 1 to 2 represent moderate to severe disability and 2 to 3 indicate severe to very severe disability.

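### The SAP's list of HAQ-DI aids leaves out the wheelchair, so a small group of wheelchair users gets no walking uplift

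*Combined protocol and SAP*

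**What the plan says.** SAP section 8.6.2.4 takes the highest item in each category as the category score, adjusts it for aids or help, and averages the categories, with at least six of the eight answered.

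The adjustment has three parts.

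- **A list of aids by category.** It opens "The aids used for adjustment by category are: dressing – devices used for dressing; rising – built up or special chars", and also covers special utensils under eating. Walking reads "walking – canes, walkers or crutches". The rest is "hygiene – raised toilet seats, bathtub seats, bathtub bars, long handles appliances in bathroom" and "reach – long-handled appliances for reaching; and grip – jar openers".
- **A general rule.** It applies when a category needs an aid, "or another person is required to help for any category then that category score increases a score of 0 or 1 to a 2". Values of 2 and 3 stay as they are.
- **An exclusion.** What participants record in the other "category will not be considered in the analysis".

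The form in Appendix A carries the instruction "Please check any AIDS OR DEVICES that you usually use for any of these activities" twice, once for each block of activities. In the first block wheelchair has its own box, in the same group as cane, walker and crutches. The form does not tie individual devices to categories. It does tie help from another person to categories, and walking is one of them.

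Protocol section 11.2.2.4 describes HAQ-DI differently, as the total divided by the number of items answered, and mentions no adjustment for aids.

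**The concern.** The aid list in section 8.6.2.4 is the only place in the documents that links a device to a category. A wheelchair is neither on that list nor an entry under other, so no rule handles a ticked wheelchair box. Yet the general rule in the same section says that a needed aid raises the category score. A programmer who codes the list gives no uplift. One who codes the general rule has to choose a category. The same data can then yield two scores.

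HAQ-DI is one of five variables of which three must improve for ACR20, ACR50 (the primary endpoint) and ACR70. It is also one of the seven MDA criteria, with a cut-off of 0.5. The protocol has the composite measures calculated automatically, so the coded list decides the result and no investigator would see the difference.

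**Working it through.** The plan states no figure on this point, so there is none to reproduce. The check has three steps.

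**1. Compare the form with the list.**

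- Form, first block: cane, walker, crutches, wheelchair, dressing devices, special utensils, special chair = 7.
- Form, second block: raised toilet seat, bathtub bar, bathtub seat, long-handled reach appliance, jar opener, long-handled bathroom appliance = 6.
- Form total, without the two Other boxes: 7 + 6 = 13.
- SAP list: dressing 1, rising 1, eating 1, walking 3, hygiene 4, reach 1, grip 1 = 12.

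The only device on the form and not on the list is the wheelchair. Every device on the list is on the form.

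**2. Effect on the score at one visit.** Let w be the walking category score and k the number of categories answered. If wheelchair counted as a walking aid, HAQ-DI would rise by (max(w, 2) − w)/k.

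| Walking score w | k = 8 | k = 6 |
|---|---|---|
| 0 | 2/8 = 0.25 | 2/6 = 0.333 |
| 1 | 1/8 = 0.125 | 1/6 = 0.167 |
| 2 or 3 | 0 | 0 |

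The rise is also zero if help with walking, a cane, a walker or crutches is ticked, because walking is then already raised to 2.

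**3. Effect on the thresholds, with eight categories answered.** S is the sum of the other seven categories. Improvement is (baseline − Week 12)/baseline, and the ACR50 component needs at least 50%. No other walking aid or help is ticked.

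| Wheelchair ticked at | Baseline S, w | Week 12 S, w | SAP list as written | Wheelchair counted |
|---|---|---|---|---|
| Both visits | 6, 0 | 3, 0 | 0.75 to 0.375: 50%, met | 1.0 to 0.625: 37.5%, not met |
| Both visits | 6, 0 | 1, 3 | 0.75 to 0.5: 33.3%, not met | 1.0 to 0.5: 50%, met |
| Baseline only | 6, 1 | total 4 | 0.875 to 0.5: 42.9%, not met | 1.0 to 0.5: 50%, met |
| Week 12 only | 6, 0 | 2, 0 | 0.75 to 0.25: 66.7%, met | 0.75 to 0.5: 33.3%, not met |

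The direction is therefore not fixed when the wheelchair is used at both visits. With use at baseline only, the omission can only hide an improvement. With use at Week 12 only, it can only create one. The same reasoning applies at 20% and 70%.

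For the MDA cut-off of 0.5, an exhaustive listing gives three cases in which the list meets the criterion and counting the wheelchair would not:

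- S = 3, w = 0: 0.375 against 0.625.
- S = 3, w = 1: 0.5 against 0.625.
- S = 4, w = 0: 0.5 against 0.75.

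**The case against.** The strongest reply is that the group affected is very narrow. The walking score is the higher of two items, level walking outdoors and climbing five steps. The gap bites only if a usual wheelchair user reports at most some difficulty on both, needs no help with walking and uses no other walking aid. Plausibly, most wheelchair users score 2 or 3. This stands.

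It also rules out several stronger readings that a reader might infer:

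- *All wheelchair users score too low.* They do not, because scores of 2 and 3 are left alone.
- *Nothing else can raise the score.* The form's box for help with walking does so, as does any other ticked walking aid.
- *Taking up or giving up a wheelchair goes unrecorded.* The tick may carry no weight, but the two walking items and the help box still respond.
- *The bias runs one way.* The examples above go both ways.

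A second reply is that the general rule on needed aids can be read to include a wheelchair, so the SAP does not clearly exclude it. That is fair: unlike entries under other, a ticked wheelchair is nowhere said to be ignored. But the general rule does not supply a category, and the list that does supply categories omits this device. The ambiguity is itself a reason to settle the rule.

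A third reply is that a changed component seldom changes an endpoint. ACR response also needs both joint counts and three of five variables, and MDA needs five of seven criteria. HAQ-DI must be the deciding variable. This stands too.

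**Conclusion.** The gap is real and small. Section 8.6.2.4, coded as written, withholds from one named device the uplift that its own general rule gives to a needed aid. With eight categories answered, HAQ-DI is lower by 0.25 or 0.125 at any visit where wheelchair is ticked, walking scores 0 or 1, and no help with walking or other walking aid is ticked. Otherwise nothing changes.

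This rests on two assumptions: that the list is coded literally, and that a wheelchair belongs under walking. Its place on the form beside cane, walker and crutches suggests the latter, but the documents do not state it.

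The documents give no number of wheelchair users, so no effect on ACR or MDA response rates can be computed. It is probably very small. A reader might infer that the ACR50 result is at risk, but the documents do not support that. The severity is the lowest.

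**What to change.** - In SAP section 8.6.2.4, add wheelchair to the walking aids, after confirming this against the instrument's scoring source. If that source says otherwise, state explicitly how a ticked wheelchair is handled.
- Use the same list in the eCOA system and in the analysis code.
- Reconcile the SAP with protocol section 11.2.2.4, which describes an item mean without adjustment for aids. SAP section 9 records the changed BASDAI derivation as a departure from the protocol but not the HAQ-DI one, and a line there would close this.

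The cost is one word in the aid list, one line of code, one look at the scoring source and one sentence in section 9. It should be settled before unblinding, because a choice made afterwards would be a post hoc decision on a component of the primary endpoint.

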**Please check any categories for which you usually need HELP FROM ANOTHER PERSON:**

- |                                                |                                  |
|------------------------------------------------|----------------------------------|
|  Dressing and Grooming |  Eating  |
|  Arising               |  Walking |

Please check the response which best describes your usual abilities OVER THE PAST WEEK:

|                              | Without
ANY
Difficulty | With
SOME
Difficulty | With
MUCH
Difficulty | UNABLE
To Do |
|------------------------------|------------------------------|----------------------------|----------------------------|-----------------|
| HYGIENE               |                              |                            |                            |                 |
| Are you able to:             |                              |                            |                            |                 |
| - Wash and dry your body?    | _____                        | _____                      | _____                      | _____           |
| - Take a tub bath?           | _____                        | _____                      | _____                      | _____           |
| - Get on and off the toilet? | _____                        | _____                      | _____                      | _____           |

|                                                                                                 |       |       |       |       |
|-------------------------------------------------------------------------------------------------|-------|-------|-------|-------|
| REACH                                                                                    |       |       |       |       |
| Are you able to:                                                                                |       |       |       |       |
| - Reach and get down a 5 pound object
(such as a bag of sugar) from just above your
head? | _____ | _____ | _____ | _____ |
| - Bend down to pick up clothing from the floor?                                                 | _____ | _____ | _____ | _____ |

|                                                |       |       |       |       |
|------------------------------------------------|-------|-------|-------|-------|
| GRIP                                    |       |       |       |       |
| Are you able to:                               |       |       |       |       |
| - Open car doors?                              | _____ | _____ | _____ | _____ |
| - Open jars which have been previously opened? | _____ | _____ | _____ | _____ |
| - Turn faucets on and off?                     | _____ | _____ | _____ | _____ |

|                                            |       |       |       |       |
|--------------------------------------------|-------|-------|-------|-------|
| ACTIVITIES                          |       |       |       |       |
| Are you able to:                           |       |       |       |       |
| - Run errands and shop?                    | _____ | _____ | _____ | _____ |
| - Get in and out of a car?                 | _____ | _____ | _____ | _____ |
| - Do chores such as vacuuming or yardwork? | _____ | _____ | _____ | _____ |

Please check any AIDS OR DEVICES that you usually use for any of these activities:

|                                                  |                                           |
|--------------------------------------------------|-------------------------------------------|
| _____ Raised toilet seat                         | _____ Bathtub bar                         |
| _____ Bathtub seat                               | _____ Long-handled appliances for reach   |
| _____ Jar opener (for jars
previously opened) | _____ Long-handled appliances in bathroom |
|                                                  | _____ Other (Specify: _____)              |

**Please check any categories for which you usually need HELP FROM ANOTHER PERSON:**

\_\_\_\_\_ Hygiene

\_\_\_\_\_ Gripping and opening things

\_\_\_\_\_ Reach

\_\_\_\_\_ Errands and chores

Appendix B: Patients Assessment of Arthritis Pain (PtAAP)

How much pain have you had because of your arthritis TODAY:

PLACE A VERTICAL (|) MARK ON THE LINE TO INDICATE THE SEVERITY OF THE PAIN.

|                 |       |                            |
|-----------------|-------|----------------------------|
| NO
PAIN
0 | _____ | MOST SEVERE
PAIN
100 |
|-----------------|-------|----------------------------|

Appendix C: Patients Global; Assessment of Disease Activity (PtAAP)

Considering all the ways your arthritis affects you, please mark a vertical line on the scale below to show how you are feeling today.

Very good  
No symptoms

0

100

Very poor  
Severe symptoms

[figure not shown]

Appendix D: Physician’s Global; Assessment of Disease Activity (PtAAP)

Please indicate your assessment of the patient’s overall disease activity by marking a vertical line through the line below.

|                                                                         |  |                                                                                                                    |
|-------------------------------------------------------------------------|--|--------------------------------------------------------------------------------------------------------------------|
| Very good,
asymptomatic and no
limitation of
normal activities |  | Very poor, very severe
symptoms which are
intolerable and inability to
carry out all normal
activities |
| 0                                                                       |  | 100                                                                                                                |

## Appendix E: Leeds Enthesitis Index (LEI)

| LEEDS ENTHESITIS INDEX (LEI)                                                |                                                                                                                                                                                                   |
|-----------------------------------------------------------------------------|---------------------------------------------------------------------------------------------------------------------------------------------------------------------------------------------------|
| 1. Date of LEI
[Date of assessment]                                      | [Date of assessment]
[Date of assessment] (DD/MM/YYYY)
 Done
Date of LEI
____/____/____
 Not Done                    |
| 2. Lateral epicondyle - Left
[Lateral epicondyle - Left]                 | [Lateral epicondyle - Left]
 Present
 Absent
 Not Done
 Not Applicable         |
| 3. Medial femoral condyle - Left
[Medial femoral condyle - Left]         | [Medial femoral condyle - Left]
 Present
 Absent
 Not Done
 Not Applicable     |
| 4. Achilles tendon insertion - Left
[Achilles tendon insertion - Left]   | [Achilles tendon insertion - Left]
 Present
 Absent
 Not Done
 Not Applicable  |
| 5. Lateral epicondyle - Right
[Lateral epicondyle - Right]               | [Lateral epicondyle - Right]
 Present
 Absent
 Not Done
 Not Applicable        |
| 6. Medial femoral condyle - Right
[Medial femoral condyle - Right]       | [Medial femoral condyle - Right]
 Present
 Absent
 Not Done
 Not Applicable    |
| 7. Achilles tendon insertion - Right
[Achilles tendon insertion - Right] | [Achilles tendon insertion - Right]
 Present
 Absent
 Not Done
 Not Applicable |
| 8. LEI score: _____                                                         | LEI score: _____                                                                                                                                                                                  |

[figure not shown]

Appendix F: Psoriatic Assessment Impact of Disease-12

We want you to indicate how much your psoriatic arthritis impacts your health. Please tell us how you have been feeling this last week.

Pain

Circle the number that best describes the pain you felt due to your psoriatic arthritis during the last week:

|      |   |   |   |   |   |   |   |   |   |   |    |         |
|------|---|---|---|---|---|---|---|---|---|---|----|---------|
| None | 0 | 1 | 2 | 3 | 4 | 5 | 6 | 7 | 8 | 9 | 10 | Extreme |
|------|---|---|---|---|---|---|---|---|---|---|----|---------|

For Office use only

Result x3

Fatigue

Circle the number that best describes the overall level of fatigue due to your psoriatic arthritis you have experienced during the last week:

|            |   |   |   |   |   |   |   |   |   |   |    |                   |
|------------|---|---|---|---|---|---|---|---|---|---|----|-------------------|
| No fatigue | 0 | 1 | 2 | 3 | 4 | 5 | 6 | 7 | 8 | 9 | 10 | Totally exhausted |
|------------|---|---|---|---|---|---|---|---|---|---|----|-------------------|

Result x2

Skin problems

Circle the number that best describes the skin problems including itching you felt due to your psoriatic arthritis during the last week:

Result x2

[figure not shown]

Statistical Analysis Plan (SAP)

[figure not shown]

None

|   |   |   |   |   |   |   |   |   |   |    |
|---|---|---|---|---|---|---|---|---|---|----|
| 0 | 1 | 2 | 3 | 4 | 5 | 6 | 7 | 8 | 9 | 10 |
|---|---|---|---|---|---|---|---|---|---|----|

Extreme

Work and/or leisure activities

Circle the number that best describes the difficulties you had to participate fully in work and/or leisure activities due to your psoriatic arthritis during the last week:

Result  
x2

|             |
|-------------|
| 

 |
|-------------|

None

|   |   |   |   |   |   |   |   |   |   |    |
|---|---|---|---|---|---|---|---|---|---|----|
| 0 | 1 | 2 | 3 | 4 | 5 | 6 | 7 | 8 | 9 | 10 |
|---|---|---|---|---|---|---|---|---|---|----|

Extreme

Functional capacity

Circle the number that best describes the difficulty you had in doing daily physical activities due to your psoriatic arthritis during the last week:

Result  
x2

|             |
|-------------|
| 

 |
|-------------|

No difficulty

|   |   |   |   |   |   |   |   |   |   |    |
|---|---|---|---|---|---|---|---|---|---|----|
| 0 | 1 | 2 | 3 | 4 | 5 | 6 | 7 | 8 | 9 | 10 |
|---|---|---|---|---|---|---|---|---|---|----|

Extreme difficulty

Discomfort

Circle the number that best describes the feeling of discomfort and annoyance with everyday tasks due to your psoriatic arthritis during the last week:

Result  
x2

|             |
|-------------|
| 

 |
|-------------|

None

|   |   |   |   |   |   |   |   |   |   |    |
|---|---|---|---|---|---|---|---|---|---|----|
| 0 | 1 | 2 | 3 | 4 | 5 | 6 | 7 | 8 | 9 | 10 |
|---|---|---|---|---|---|---|---|---|---|----|

Extreme

[figure not shown]

Sleep disturbance

Circle the number that best describes the sleep difficulties (i.e., resting at night) you felt due to your psoriatic arthritis during the last week:

|               |   |   |   |   |   |   |   |   |   |   |    |                    |
|---------------|---|---|---|---|---|---|---|---|---|---|----|--------------------|
| No difficulty | 0 | 1 | 2 | 3 | 4 | 5 | 6 | 7 | 8 | 9 | 10 | Extreme difficulty |
|---------------|---|---|---|---|---|---|---|---|---|---|----|--------------------|

|           |                          |
|-----------|--------------------------|
| Result x2 |  |
|-----------|--------------------------|

Coping

Considering your psoriatic arthritis overall, how well did you cope (manage, deal, make do) with your psoriatic arthritis during the last week?

|           |   |   |   |   |   |   |   |   |   |   |    |             |
|-----------|---|---|---|---|---|---|---|---|---|---|----|-------------|
| Very well | 0 | 1 | 2 | 3 | 4 | 5 | 6 | 7 | 8 | 9 | 10 | Very poorly |
|-----------|---|---|---|---|---|---|---|---|---|---|----|-------------|

|                     |           |                          |
|---------------------|-----------|--------------------------|
| For Office use only | Result x1 |  |
|---------------------|-----------|--------------------------|

Anxiety, fear and uncertainty

Circle the number that best describes the level of anxiety, fear and uncertainty (for example about the future, treatments, fear of loneliness) due to your psoriatic arthritis you have experienced during the last week:

|      |   |   |   |   |   |   |   |   |   |   |    |         |
|------|---|---|---|---|---|---|---|---|---|---|----|---------|
| None | 0 | 1 | 2 | 3 | 4 | 5 | 6 | 7 | 8 | 9 | 10 | Extreme |
|------|---|---|---|---|---|---|---|---|---|---|----|---------|

|           |                          |
|-----------|--------------------------|
| Result x1 |  |
|-----------|--------------------------|

Embarrassment and/or shame

Considering your psoriatic arthritis overall, circle the number that best describes the level of embarrassment and/or shame due to your appearance experienced during the last week:

|           |                          |
|-----------|--------------------------|
| Result x1 |  |
|-----------|--------------------------|

[figure not shown]

|      |   |   |   |   |   |   |   |   |   |   |    |         |
|------|---|---|---|---|---|---|---|---|---|---|----|---------|
| None | 0 | 1 | 2 | 3 | 4 | 5 | 6 | 7 | 8 | 9 | 10 | Extreme |
|------|---|---|---|---|---|---|---|---|---|---|----|---------|

Social participation

Circle the number that best describes the difficulties you had to participate fully in social activities (including relationships with family and/or people very close to you) due to your psoriatic arthritis during the last week:

|                      |
|----------------------|
| Result
x1         |
|  |

|      |   |   |   |   |   |   |   |   |   |   |    |         |
|------|---|---|---|---|---|---|---|---|---|---|----|---------|
| None | 0 | 1 | 2 | 3 | 4 | 5 | 6 | 7 | 8 | 9 | 10 | Extreme |
|------|---|---|---|---|---|---|---|---|---|---|----|---------|

Depression

Circle the number that best describes the level of depression due to your psoriatic arthritis you have experienced during the last week:

|                      |
|----------------------|
| Result
x1         |
|  |

|      |   |   |   |   |   |   |   |   |   |   |    |         |
|------|---|---|---|---|---|---|---|---|---|---|----|---------|
| None | 0 | 1 | 2 | 3 | 4 | 5 | 6 | 7 | 8 | 9 | 10 | Extreme |
|------|---|---|---|---|---|---|---|---|---|---|----|---------|

THANK YOU FOR ANSWERING THIS QUESTIONNAIRE

|                                                   |
|---------------------------------------------------|
| Final PsAID out of
20                          |
| Add up the  and divide by 20: |

